## Abstract

**Introduction:**

Depression and anxiety are common in dementia, with a devastating impact. However, there remains a lack of evidence-based psychological therapies for this clinical group. Compassion-focused therapy (CFT), a talking therapy which addresses feelings of shame and stigma, has shown benefits in other clinical populations. This study is a mixed-methods feasibility randomised controlled trial (RCT) of group CFT for people with dementia and symptoms of anxiety and/or depression, to determine if a future definitive RCT is feasible.

**Methods and analysis:**

50 people with mild-to-moderate dementia and symptoms of anxiety and/or depression will be randomised to either the intervention arm (12 sessions of group CFT plus treatment as usual (TAU)) or the control arm (TAU). Primary outcome measures include the feasibility of conducting an RCT in terms of recruitment, acceptability, suitability of secondary outcome measures and fidelity. Blind assessments will be conducted at baseline, approximately 16 weeks and 6 months follow-up, to collect data on depression, anxiety, quality of life, quality of the carer–patient relationship, cognition, self-compassion and carer burden. Qualitative interviews will be used to gather participant, carer/supporter and clinician perspectives on the value, acceptability and feasibility of the intervention.

**Ethics and dissemination:**

This study has been approved by the London Riverside REC (Ref: 23/LO/0535) and the Health Research Authority (HRA) ethical approval process through the Integrated Research Application System (IRAS ID: 327086). We plan to publish the results in open-access peer-reviewed journals, present data at conferences and provide feedback to the study participants, sponsors and funders.

**Trial registration number:**

ISRCTN20868432.

STRENGTHS AND LIMITATIONS OF THIS STUDYA strength is the mixed-methods approach, enabling triangulation of information to enhance the reliability and validity of our findings.Given that people with dementia might lack technology, Wi-Fi, transport provision or have comorbid health or mobility problems, a strength of this study is offering the choice of virtual or face-to-face attendance.A strength is our inclusive approach, recruiting from an underserved research area, Barking and Dagenham, which has the highest ‘Index of Multiple Deprivation’ score in London and 21/317 in England.A potential limitation is the availability of psychologists to deliver the intervention, preventing some Trusts from being able to take part as research sites.

## Introduction

 Depression and anxiety are common in dementia and can have a devastating impact including accelerated cognitive decline, increased need for institutional care and premature death. There are currently no pharmacological or psychological therapies with established efficacy for these individuals, presenting a critical gap in both treatment and care. A meta-analysis^1^ suggested that psychosocial treatments for both depression and anxiety in people with dementia are limited, but they provide an important avenue of likely benefit.

Compassion-focused therapy (CFT)^2^ is a talking therapy that integrates techniques from evolutionary, social and developmental psychology. It focuses on reducing self-criticism and shame, acknowledging the emotional impact of difficult experiences, building compassion for the self and others and facilitating adjustment and acceptance. The theoretical stance lends itself well to those with mild-to-moderate dementia, for whom stigma can result in shame, embarrassment and self-criticism.^3^ CFT specifically addresses how people with dementia respond to their cognitive deterioration. Developing acceptance is likely to facilitate adjustment and be emotionally protective, ultimately reducing clinical depression and anxiety and improving well-being.

Our team ([name] *et al*^4^) systematically reviewed the effectiveness of CFT in clinical populations including depression, psychosis and borderline personality disorder. This included 15 studies (4 randomised controlled trials (RCTs)), finding significant improvements in symptomatology and self-compassion. CFT was acceptable and feasible to deliver in clinical settings, especially when delivered in a group format over at least 12 hours. The review concluded that CFT shows promise for a range of conditions, with RCT evidence urgently needed. We also ([name] *et al*^5^) developed and evaluated a 10-session manualised CFT intervention for dementia. This CFT case series (n=7) found clinically significant changes in depression (n=4) and anxiety (n=3), highlighting feasibility and potential. While this work^5^ focused on individual CFT sessions, there are strong economic and practical arguments for group delivery within the National Health Service (NHS).

This study aims to evaluate the feasibility, acceptability and fidelity of 12 sessions of group CFT as a treatment for people with dementia experiencing anxiety and/or depression. Blind assessments will be conducted at baseline, approximately 16 weeks and 6 months follow-up, to collect data on depression, anxiety, quality of life, quality of the carer–patient relationship, cognition, self-compassion and carer burden. Qualitative interviews will be used to gather participant, carer/supporter and clinician perspectives on the value, acceptability and feasibility of the intervention. Results of this study will determine if a full RCT is warranted.

## Methods and analysis

### Trial design

A single-blind feasibility RCT will compare group CFT plus treatment as usual (TAU) against TAU alone. 50 participants will be randomised to either the intervention group (CFT plus TAU) or control group (TAU). Randomisation will occur after baseline assessments are completed. Each arm will have approximately 25 participants, with up to 7 participants in each CFT group. The duration of the intervention will be 15 weeks, consisting of 12 hourly CFT therapy sessions. The 15-week block is being used to hold 12 sessions of CFT, to provide a buffer to allow for factors such as weather issues, therapist annual leave and illness, increasing the likelihood that participants will receive all 12 sessions. There will be assessments at baseline, during the 2 weeks prior to randomisation, at the end of the intervention at approximately 16 weeks and at 6 months follow-up.

To further inform our understanding of the process and feasibility of implementation, we will conduct semistructured, audiorecorded qualitative interviews with up to 20 participants with dementia, 15 carers/supporters and 10 NHS personnel (including group facilitators and service managers). These will provide insight into the feasibility of implementation and explore trial procedures from the perspectives of those who did and did not participate in the intervention or carers workshop and barriers to attendance.

### Study timelines

The study duration is 30 months, and the start date was 1 April 2023. Recruitment opened at NELFT on 8 November 2023 and we expect recruitment to be complete by the end of 2024 to allow time for the 6 months follow ups. Data cleaning and analysis will take place between April and October 2025.

### Sample size

This is a feasibility study with no formal power calculation. Instead, a sufficient number of participants need to be recruited in order to determine the attrition and recruitment rates and how these are related to feasibility of a full-scale RCT. By setting our target sample size at 50, we will achieve adequate precision around our expected retention rate of 75% (95% CI 62% to 86%) to determine feasibility going forward. In addition to the sample size of 50 people with dementia, each site will be expected to recruit and consent carers/supporters into the trial, as they will be contributing to the quantitative data collection. We will conduct qualitative interviews with up to 20 people with dementia, up to 15 carers/supporters and up to 10 NHS personnel. Consent will be required before any qualitative interview can take place.

### Recruitment of participants

Participants are currently being recruited and enrolled to the study. Recruitment will primarily take place through the NHS Foundation Trusts of North East London, Oxford Health, Norfolk and Suffolk, the Black Country Healthcare, Central and North West London, Lincolnshire Partnership and Cheshire and Wirral Partnership.

Recruitment will be conducted in adherence with local Trust privacy notice permissions and consent to contact arrangements. The study will be promoted through relevant services and routes specific to the local Trust including non-NHS pathways such as third-sector organisations, supported living accommodation and care homes. We will recruit through ‘Join Dementia Research’, an online recruitment platform. ‘Join Dementia Research’ recruitment can only be from within the locality of the Trusts involved.

Participants will be approached by the recruiting team to discuss the study with the participant and their carer/supporter (where available and willing). If they are interested in taking part, both the participant and their carer/supporter (if applicable) will be provided with a relevant information sheet. A participant information sheet is included as online supplemental material file 1. If interested, the research team will arrange a meeting to answer questions and assess eligibility. If the participant and carer/supporter (if applicable) agree to take part, consent can be received either in person (in writing) or remotely (verbally). Two participant consent forms are provided as onlinesupplemental material files 2  3.

Inclusion criteria are as follows:

Meet Diagnostic and Statistical Manual of Mental Disorders, Fourth Edition for dementia of any type.^6^Mild-to-moderate dementia as determined by the Clinical Dementia Rating Scale.^7^Experience symptoms of depression and/or anxiety (≥8) as measured by the Hospital Anxiety and Depression Scale (HADS)^8^ or a minimum score of 5 and experience of depression and/or anxiety as reported by either the caregiver or clinician.Have the capacity to consent to take part in research.Can communicate in English.Have access to WiFi, enabling them to partake in online CFT groups or the ability to attend a face-to-face group.Are not participating in another interventional research programme concurrently.Aged 18 and over.People can be included whether or not they have a caregiver.

No age, care situation or access to teleconferencing devices exclusion criteria will be applied.

### Randomisation procedures and blinding

Participant randomisation will be undertaken remotely via a secure online system using a dynamic adaptive randomisation algorithm provided and maintained by the Clinical Trials Unit NWORTH, Bangor University^9^. Participants will have indicated whether they are able to attend face to face only, online only or can attend either session format (in addition to their preference) when they provide consent. From this, the researcher will construct ‘randomisation blocks’ based on their ability to attend either format. Once the recruiting site reaches approximately 10 recruits to a ‘randomisation block’ (ie, online or face to face), the randomisation procedure will be carried out. If there are too few participants at one site that can only attend online, then the online groups may be combined with other sites including participants from ‘Join Dementia Research’ to form one online group. The minimum number in each CFT group is 3 participants, with the maximum being 7. The results of the randomisation will be sent to the unblinded researcher and relayed to the participants, arrangements can then be made to begin the intervention or for TAU. The intervention should begin within a week of randomisation.

Due to the nature of the intervention, it is not possible to blind participants, however, researchers collecting outcome data will be blinded. As participants may accidentally unblind researchers during follow-up assessments, we will collect data on the occasions where this happens and where possible a different researcher will conduct future assessments. The trial statistician will remain blind throughout the duration of the study until the blinded analysis (detailed in the analysis plan) has been conducted and reported to the study team.

### Intervention

The intervention comprises 12 virtual or face-to-face group CFT sessions, each lasting 60 minutes, divided into three phases:

Phase 1: Introduction to CFT, psychoeducation on emotion regulation systems, formulation and goal setting.Phase 2: Techniques for developing self-compassion, including imagery and writing compassionate letters to self.Phase 3: Techniques to tolerate difficult feelings, focusing on maintaining benefits post intervention.

Sessions will include core CFT practices, for example, ‘soothing rhythm breathing’ and will introduce new concepts, such as the qualities of compassion and mindful awareness. Participants will reflect on the emotional experience of living with dementia, such as the ‘threat’ posed by the diagnosis to their sense of self and future, leading to fear, anxiety and disconnection. Sessions will conclude with suggestions for home practice, with participants receiving session summaries. CFT will be adapted to accommodate cognitive changes, with frequent repetition and the use of visual and verbal aids. Building on the experience of running Cognitive Stimulation Therapy (CST) groups,^10^ groups will consist of approximately five people and where possible there will be time for social interaction before and after the session.

Additional carer/supporter workshop: We will run a brief workshop (flexibility for online or face to face) for primary carers/supporters (if available) towards the beginning of the CFT programme. This workshop will educate carers/supporters on CFT principles, outline session content and offer tips for encouraging and supporting the therapy at home.

The intervention group will continue to have access to TAU (see description below). As both groups will have access to TAU, this study will look at the additional impact of CFT. For those who do not own a tablet and wish to complete the online intervention, 10 tablets will be purchased and lent to those participants, aiming to maximise inclusivity.

### Treatment as usual

TAU is defined as standard treatment available to people with dementia and depression and/or anxiety, which might include medication, other therapies, day care, input from health and social care professionals such as psychiatrists, psychologists and social workers or no treatment. We will collect information on all health and care services used by people with dementia (which we can compare with ongoing observational studies such as IDEAL^11^) to describe what TAU involves for each participant; this can be taken into account in a future, fully powered trial.

### Primary outcome measures

#### Feasibility outcomes

1. Feasibility of recruitment and retention, assessed by:

1.1. Successful recruitment of the target sample (50 people) in 14 months.

1.2. Retention rate of at least 75% of participants to 16-week follow-up.

2. Acceptability of the intervention, assessed by:

2.1. Overall attendance and retention rates among the CFT participants (over 60%).

2.2. Any negative or adverse events (AEs) related to the intervention.

2.3. Preference of virtual or face-to-face therapy.

3. Fidelity, assessed by:

3.1. Therapist completion of the fidelity checklist following each session.

3.2. Audio recording of all sessions and an independent researcher rating fidelity with a random 10% of the recordings. A total, mean fidelity score and percentage will be calculated for each CFT session. These scores will be compared across sites and providers. We will compare self-reports with observer ratings, providing some idea about the utility of self-reports in a future trial.

Feasibility of progression to a definitive RCT will be assessed on a ‘Stop/Review/Go’ basis, with a successful outcome being that all criteria are assessed as ‘Go’. Continuation will still be possible with a combination of ‘Review’ and ‘Go’ flags but will require additional discussion about how to proceed. Any ‘Stop’ criteria will indicate that either the design or processes will need to be overhauled and would indicate any future work would involve further piloting.

Indicative criteria would be:

Recruitment of participants within 14 months: Go: ≥90%, review: 60%–89%, stop: <60%.Retention of participants at 6 months: Go: ≥75%, review: 45%–74%, stop: <45%.Number of sessions delivered: Go: ≥90%, review: 70%–89%, stop: ≤70%.Participant attendance at sessions delivered: Go: >80%, review: 50%–79%, stop: ≤50%.Collection of outcome data at a time point: Go: ≥80%, review 55%–79%, stop: <55%.

The flow of participants in the study will be summarised using a Consolidated Standards of Reporting Trials flow diagram. From this data, some of the primary outcome measures will be calculated, such as eligibility and retention rates and willingness to be randomised (randomisation/recruitment rate).

Acceptability of the intervention to clinicians and participants will be assessed both qualitatively and quantitively. Access to technology, ability to collect outcome data and retention of the intervention will be presented descriptively from data collected in the electronic case report forms (CRFs). Access to technology and availability to travel will be assessed as part of the initial screening session by the local researcher. The research team will record ability to collect outcome data and retention of the intervention.

Preliminary efficacy of the intervention will be assessed using the quantitative measures outlined below, all with good to excellent psychometric properties, by a researcher blind to group allocation, at week zero (baseline), approximately 16 weeks and 6 months. Suitability of secondary outcome measures for a definitive RCT will be established by analysis of completion and response rates, outcome sensitivity to change as a result of the intervention and qualitative findings as to the perceived benefits and their relative importance.

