### Statistical analysis

A statistical analysis plan will be written, agreed and signed off before data lock is complete detailing all quantitative analysis to be conducted by NWORTH. Primary analysis will be based on the feasibility outcomes defined above. For the proposed clinical outcomes, we will conduct exploratory statistical analyses using ‘intention-to-treat’ principles. The focus of the results will be on the estimates of the treatment effects rather than statistical significance. Therefore, differences between the two comparison groups will be presented in the form of an unadjusted mean difference for continuous outcomes, and an OR for binary outcomes, with their associated 95% CIs. Given the nature of this study, no imputation methods will be used over and above any rules indicated by the measures for handling missing items. Missing data will be used to assess the suitability of the measure’s future use. Despite individual randomisation, the treatment is group based, and therefore, we will estimate the potential ICC coefficient. This, together with indications from other work, will guide the sample size of a future trial.

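### Attendance at group CFT has two unreconciled thresholds: over 60% as a primary acceptability outcome, but over 80% for Go

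*Protocol article*

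**What the plan says.** The protocol article gives two attendance thresholds for the CFT arm, both under Primary outcome measures, Feasibility outcomes.

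- Item 2.1, listed under acceptability of the intervention: "Overall attendance and retention rates among the CFT participants (over 60" (a percentage). One figure covers both attendance and retention.
- The progression criteria: "Participant attendance at sessions delivered: Go: >80%, review: 50%–79%, stop: ≤50" (again a percentage).

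The progression rule describes itself as "with a successful outcome being that all criteria are assessed as ‘Go". A mixture of flags is not fatal: "Continuation will still be possible with a combination of ‘Review’ and ‘Go’ flags but will require additional discussion about how to proceed". The list of bands is introduced by "Indicative criteria would be". The Statistical analysis section then states: "Primary analysis will be based on the feasibility outcomes defined above".

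The article does not say how the 60% relates to the 80%, or which denominator overall attendance uses.

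**The concern.** Acceptability of the intervention is one of the three groups of primary feasibility outcomes, and attendance is its main numerical component. If the two thresholds measure the same thing, there is a wide range in which the trial can report that its acceptability outcome was met while its own progression rule says that attendance did not reach the level needed for success. There is also a lower range in which the acceptability outcome is missed but the progression rule raises nothing stronger than Review.

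Threshold rules of this kind are written in advance so that the conclusion does not depend on who reads the result. With two figures and no rule between them, the team can choose the favourable one after seeing the attendance registers.

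**Working it through.** **Inputs.** From Feasibility outcomes: item 2.1 is met if attendance exceeds 60%; Go is above 80%, Review is 50%–79%, Stop is 50% or below. From Trial design: "Each arm will have approximately 25 participants, with up to 7 participants in each CFT group". From Intervention: "The intervention comprises 12 virtual or face-to-face group CFT sessions, each lasting 60 minutes".

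**The plan's own figure.** Neither 60% nor 80% is derived anywhere. The one computed figure is the 95% CI of 62% to 86% around 75% retention with n = 50. It can be reproduced: a Wald interval at 37/50 is 0.74 ± 1.96 × √(0.74 × 0.26/50), which gives 61.8% to 86.2%. It has no bearing on attendance.

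**Step 1: same denominator.** Classify attendance *a* under each rule.

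| Attendance *a* | Item 2.1 | Progression band |
|---|---|---|
| below 50% | not met | Stop |
| exactly 50% | not met | Stop and Review |
| above 50%, up to 60% | not met | Review |
| above 60%, up to 79% | met | Review |
| above 79%, up to 80% | met | none |
| above 80% | met | Go |

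The two rules agree on success only above 80%. Rounding to whole percentages does not close the gap, because 80% is neither above 80% nor within 50%–79%.

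**Step 2: size in sessions.** Assume exactly 25 CFT participants, all 12 sessions delivered and everyone counted: 25 × 12 = 300 person-sessions.

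- Item 2.1: 0.60 × 300 = 180, so at least 181 are needed.
- Go: 0.80 × 300 = 240, so at least 241 are needed.
- Totals of 181 to 240 (60 values) meet item 2.1 without being Go. Since 0.79 × 300 = 237, totals of 181 to 237 are Review, and 238, 239 and 240 have no band.
- Since 0.50 × 300 = 150, totals of 151 to 180 fail item 2.1 yet are Review.

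In mean sessions per person, the conflict zone runs from 0.60 × 12 = 7.2 to 0.80 × 12 = 9.6.

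**Step 3: different denominators.** Suppose overall attendance counts planned sessions and the band counts delivered sessions. If a share *d* of sessions is delivered, the Go boundary is 0.80 × *d* of planned sessions.

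- *d* = 90%, the lowest value rated Go for delivery: 0.80 × 0.90 = 72%. The overlap is 60%–72% of planned sessions.
- *d* = 75%: 0.80 × 0.75 = 60%. The overlap vanishes, but 75% delivery is itself only Review.

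So whenever delivery is Go, some overlap remains.

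**Step 4: can a relation be inferred from the other pairs?** Recruitment item 1.1 asks for all 50 people (100%), which is stricter than its Go level of 90%. Retention item 1.2 asks for 75%, the same figure as its Go level, although at 16 weeks rather than 6 months. Attendance item 2.1 asks for 60%, looser than its Go level and inside the Review band. The pairs are stricter, equal and looser in turn, so they show no consistent rule.

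**The case against.** The strongest reply is that the two figures answer different questions. Item 2.1 is about whether the therapy is acceptable; the bands are about whether to proceed to a definitive trial, and they are only indicative. A lower bar for acceptability and a higher one for unqualified progression would be coherent, and acceptability is also to be judged qualitatively. This is a possible reading, but the article does not state it, and Step 4 shows that the other pairs do not follow it.

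A second reply is that the quantities differ. Overall attendance may include sessions that were not held or people who left therapy. This stands as a possibility. It narrows the overlap, as in Step 3, but does not remove it while delivery is rated Go. The analysis plan, which is not shown, may define denominators, but it would still have to choose between two published figures or state how they relate.

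A reader might also infer that the plan returns opposite verdicts between 60% and 80%. It does not. The opposite of meeting item 2.1 would be Stop, and no attendance above 60% is Stop; Review leaves continuation open.

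Nor do the documents support reading item 2.1 as a 60% retention bar that contradicts the 75% bar for the whole trial. Item 1.2 concerns retention to follow-up, whereas item 2.1 sits under acceptability of the intervention. The Discontinuation/withdrawal section separates leaving the intervention from leaving follow-up and asks those who leave therapy to continue providing data. Different bars for those two quantities are not inconsistent.

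**Conclusion.** The point holds as an unreconciled pair of pre-specified thresholds on a primary feasibility outcome. With a common denominator, the rules disagree on success for attendance above 60% and up to 80%. They are also out of step above 50% and up to 60%, where the primary outcome is missed but the flag is only Review. Two edge values are faulty whatever the 60% means: attendance above 79% and up to 80% has no band, and exactly 50% has two.

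The figure of 181 to 240 out of 300 rests on 25 participants (the article says approximately 25), full delivery and a shared denominator. The 60%–72% range rests on a planned-sessions denominator and 90% delivery. The article gives no attendance data, so how likely attendance is to fall in these ranges cannot be judged.

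This should be fixed, but it is not critical. Progression can still follow the bands, and no treatment estimate or sample size depends on the 60%.

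**What to change.** Before data lock, and preferably before attendance is tabulated:

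1. Make the Stop/Review/Go band the single attendance criterion and state its denominator once: planned or delivered sessions, and all CFT participants or only those still in therapy.
2. Remove the 60% figure from attendance in item 2.1. If 60% was meant for staying in therapy, list that as a separate criterion with its own numerator and denominator, distinct from the 75% follow-up retention.
3. Close the band edges so that every value from above 79% to 80% has a band and exactly 50% has only one.

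The change is confined to wording in the protocol or analysis plan. The downside is that, if the bar of over 80% is kept, the acceptability claim becomes harder to meet than under item 2.1 as it stands.

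### Two of the five indicative Stop/Review/Go criteria do not divide the percentage scale: 70% of sessions delivered and 50% attendance are both Review and Stop, and 80% attendance has no band

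*Protocol article*

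**What the plan says.** The protocol article, under Primary outcome measures (Feasibility outcomes), introduces five progression criteria with "Indicative criteria would be". The two at issue, each ending in a percentage sign, are:

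- "Number of sessions delivered: Go: ≥90%, review: 70%–89%, stop: ≤70"
- "Participant attendance at sessions delivered: Go: >80%, review: 50%–79%, stop: ≤50"

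The other three are:

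- "Recruitment of participants within 14 months: Go: ≥90%, review: 60%–89%, stop: <60"
- "Retention of participants at 6 months: Go: ≥75%, review: 45%–74%, stop: <45"
- "Collection of outcome data at a time point: Go: ≥80%, review 55%–79%, stop: <55"

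The same section says what each class leads to. Success is Go on every criterion. For mixed results, "Continuation will still be possible with a combination of ‘Review’ and ‘Go’ flags but will require additional discussion about how to proceed". For the lowest class, "Any ‘Stop’ criteria will indicate that either the design or processes will need to be overhauled", and future work would then be more piloting. The article gives no rounding rule and no rule for a value that meets two bands or none.

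**The concern.** A progression rule should send each possible result to exactly one class. Here two results meet the definitions of both Review and Stop, and one meets none.

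The overlaps carry the greater weight, because the two classes lead to different decisions: continue after discussion, or rework the design or processes and pilot again. At 80% attendance the rule cannot say whether the success condition, Go on every criterion, has been met.

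The Statistical analysis section bases the primary analysis on the feasibility outcomes, and the Abstract gives the purpose as judging whether a definitive trial is feasible. If a result fell on one of these edges, its class would have to be chosen after the result was known, which fixing criteria in advance is meant to prevent.

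**Working it through.** There is no stated power, sample size or interval to reproduce for this point. The check is whether each row, read literally, assigns every whole percentage from 0 to 100 to exactly one class.

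**Step 1: classify the whole percentages**

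| Criterion | Go | Review | Stop | In two bands | In no band |
|---|---|---|---|---|---|
| Recruitment | ≥90 | 60–89 | <60 | none | none |
| Retention at 6 months | ≥75 | 45–74 | <45 | none | none |
| Sessions delivered | ≥90 | 70–89 | ≤70 | 70 | none |
| Attendance | >80 | 50–79 | ≤50 | 50 | 80 |
| Outcome data | ≥80 | 55–79 | <55 | none | none |

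There are three faulty values, in two rows. The three sound rows share one pattern: Go is at or above its edge, and Stop is strictly below the start of Review. The sessions row departs from it at Stop, and the attendance row at both Go and Stop.

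**Step 2: can the faulty values occur?**

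Inputs: about 25 participants per arm (Trial design); groups of about five, 12 sessions per group (Intervention).

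*Sessions delivered.* With g groups, 12g sessions are planned, and 70% of them is 0.70 × 12g = 8.4g. This is a whole number only when g is a multiple of 5.

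- g = 5 (assumed from 25/5): 60 sessions, 42/60 = 70.0%, both Review and Stop.
- g = 4: 48 sessions, 8.4 × 4 = 33.6. The nearest results are 33/48 = 68.8% and 34/48 = 70.8%, so 70% does not occur, even after rounding.
- g = 6: 72 sessions, 8.4 × 6 = 50.4. The nearest results are 50/72 = 69.4% and 51/72 = 70.8%, so again it does not occur.

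*Attendance.* Assuming 25 participants and all 12 sessions delivered, there are 25 × 12 = 300 possible attendances.

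- 150/300 = 50.0%, both Review and Stop.
- 240/300 = 80.0%, no band.

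The denominator will differ if sessions are cancelled or the arm is not exactly 25. Exactly 50% needs an even denominator, and exactly 80% needs one divisible by 5.

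**Step 3: does rounding to whole percentages remove the faults?**

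It does not. For attendance it widens them:

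- 149, 150 and 151 of 300 (49.7%, 50.0%, 50.3%) all round to 50%, which has two classes.
- 239, 240 and 241 of 300 (79.7%, 80.0%, 80.3%) all round to 80%, which has none.

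Without rounding, 150 of 300 has two classes, and 238, 239 and 240 of 300 (79.3%, 79.7%, 80.0%) have none.

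**Step 4: apply the pattern of the sound rows to the two faulty ones**

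With sessions delivered at Stop <70%, and attendance at Go ≥80% and Stop <50%, every whole percentage falls in exactly one class in all five rows.

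**The case against.** The strongest reply is that the criteria are called indicative, so they guide a discussion and do not bind anyone. The faults sit at three edge values, and no estimate, sample size or safety decision depends on them. The 70% edge for sessions also needs a number of groups that is a multiple of five, and the 15-week window for 12 sessions (Trial design) is there to make full delivery likely. All of this stands and keeps the point minor. It does not make the text consistent: even an indicative threshold has to place a result in one class.

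A reader might infer that all five criteria are defective, because an unrounded value such as 43/48 = 89.6% sessions, 39/49 = 79.6% outcome data or 35/47 = 74.5% retention lies between the printed bands. The article does not support that reading. Bands printed in whole percentages are ordinary notation, and rounding places these values at 90% (Go), 80% (Go) and 74% (Review). With 50 participants, recruitment, retention and outcome data move in steps of 2 percentage points and never fall between bands: recruitment, for example, goes from 44/50 = 88% to 45/50 = 90%. The absence of a rounding rule is worth one sentence in the plan, but it is not a fault in those three rows.

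A reader might also infer that the 80% attendance gap puts a Stop decision in doubt. It does not. The gap lies between Review and Go, and both allow continuation.

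**Conclusion.** The point holds for two of the five criteria and three values: 70% of sessions delivered (Review and Stop), 50% attendance (Review and Stop) and 80% attendance (no class). The first two leave open whether the result is Review or Stop; the third leaves open only whether the success condition is met. That the values can occur rests on assumptions the article makes plausible but does not fix: five groups for the sessions edge, and 25 participants with every session delivered for the figures out of 300.

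Severity is minor. A reader might take the contradiction as grounds to treat the whole progression scheme as unusable, but the indicative status, the narrow edges and the three sound rows do not support that. Nor does the article settle which class was meant at each edge. The three sound rows point to Review at 70% and at 50%, and Go at 80%, but starting Review just above 70% and 50%, or extending it to 80%, would also be coherent.

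**What to change.** Before delivery and attendance totals are seen, and at the latest in the statistical analysis plan that is to be signed off before data lock, restate the two rows in the pattern of the other three:

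- Sessions delivered: Go ≥90%; Review ≥70% to <90%; Stop <70%.
- Attendance at sessions delivered: Go ≥80%; Review ≥50% to <80%; Stop <50%.

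If the authors intend a different class at 70%, 50% or 80%, they should state it instead. Add one sentence saying whether percentages are rounded before classification; that settles values between bands in all five rows. The other three rows need no other change.

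The cost is wording only, with no effect on recruitment, data collection or conduct.
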